### Definition of study conclusion

The study is expected to conclude by August 2025. The last patient may be enrolled by July 2024. Investigators must not implement any deviation or modification of the Clinical Trial Protocol without prior favorable opinion from the ethics committee.

## Discussion

Over the last decades, several interventions have been developed to improve reading skills in children and adolescents with DD (8, 9), although with poor results in term of efficacy and long-term achievements. The growing understanding of the neurobiology of reading in individuals with and without DD has led to the exploration of brain-directed methods as a potential new frontier in the treatment of DD.

Promising findings on the application of tES to improve reading in individuals with DD are already available and represent the rationale for this project (23). However, there is still a need to bridge the gap and reduce the variability in results, thereby optimizing neuromodulation protocols. This includes identifying the most effective technique to employ.

The present study aims to compare two tES techniques already used in pediatrics, namely tDCS and hf-tRNS, to investigate (i) which is more effective in improving reading abilities in children and adolescents with DD, and (ii) which is the most suitable in terms of safety and tolerability.

tDCS is definitely the most widely used technique to ameliorate reading performance in DD. One of the reasons is that numerous investigations have allowed to determine reliable tDCS parameters in terms of intensity and duration to achieve plastic after-effects, particularly by combining tDCS with transcranial magnetic stimulation at the level of the motor cortex (28). Moreover, tDCS polarity-dependent nature resulted suitable for left-hemisphere lateralization of reading [i.e., hypoactivation of a left hemisphere brain network and hyperactivation of contralateral homologous regions; for a review, see (6)], considering the possibility to simultaneously manipulate excitation/inhibition balance, via anodal/cathodal montage over target brain areas. Consistently, we will employ the left anodal/right cathodal montage accordingly to several studies that demonstrated the superiority of this montage in improving reading performance (23). Specifically, we will target the temporo-parietal regions that are crucially involved in reading, particularly in the process of letter-to-sound conversion (66–68).

Conversely, tRNS is a polarity-independent form of tES that employs the same electrode arrangement as tDCS to boost neuronal activity, but uses both electrodes to increase cortical excitability (28, 31). Previous findings have shown stronger effects of tRNS compared to tDCS on language and learning abilities, including mathematical skills (69), as well as on other cognitive (26, 27, 35, 36) and perceptual processes (39).

Our selection of tES parameters, including intensity, density, duration, and frequency, will be based on previous research demonstrating the safety and beneficial effects of these parameters on reading performance (16–22) and cognitive tasks (24, 60, 63, 70, 71).

Concerning tDCS, we will employ a tDCS set-up that delivers a constant current at 1 mA intensity for 20 min. This configuration aligns with previous studies that have demonstrated the safety and tolerability of this approach in pediatric populations (16–22).

As for hf-tRNS, we will apply a current intensity of 75% of 1 mA. The choice to administer a 75% of 1 mA current was reached considering the parameters that affect the distribution and concentration of current at the stimulation site. These factors include a reduced thickness of the scalp, decreased cerebrospinal fluid volume, and the comparatively smaller head dimensions in the pediatric population (72–74). Concerning the frequency band, tRNS can administer current in three distinct frequency ranges: a full-frequency range (typically spanning from 0.1 to 640 Hz), a low-frequency range (typically ranging from 0.1 to 100 Hz), and a high-frequency range (typically ranging from 101 to 640 Hz). Our decision to use the hf-tRNS set-up is based on evidence demonstrating that only at 100–500 Hz of frequency tRNS provides consistent and long-lasting cortical excitability (31).

With respect to the experimental design, the choice of a within-subjects design is motivated by the aim to reduce inter-subject variability, which is well-known in the effects of tES [for a review, see (75)]. Within-subjects designs offer comparable accuracy to between-subjects designs and enhance statistical power even with a smaller number of participants (76–78) and suppressing inter-subject variability (79, 80). In between-subject designs, there is a greater risk that stable factors specific to each participant may influence responses to tES conditions. In particular, it has been demonstrated that individuals anatomical differences (e.g., skull thickness, cortex morphology, and gyrification) could influence the electric field reaching the brain (74, 81, 82), and consequently modulate the behavioral effects of tES. Moreover, several studies showed that individual’s genotype seems to modulate synaptic plasticity and neurotransmitters expression, somehow affecting the effects of tES (83). Furthermore, it has been found that major demographic characteristics such as gender (84, 85) and age (83–85) could contribute to the inter-subject variability in the effects of tES.

Among the main purposes of the present study is to compare the safety and tolerability profile of tDCS and tRNS in pediatrics, in order to verify which intervention is safer and more suitable for use as standard-of-care intervention for children and adolescents with DD. While tES has been increasingly applied in developmental age, there are limited studies that have systematically investigated the safety and tolerability of tES in children and adolescents [(40, 86–88); for a review, see (41)], overall promoting tES as a safe method as for adults. Furthermore, while evidence suggests that tRNS is a safe and potentially less perceptible technique compared to tDCS (26, 36, 38), only one study has directly compared the safety and tolerability of the two techniques in children and adolescents (26), demonstrating that tRNS is less perceptible and potentially preferable in pediatrics. In particular, Berger et al. (26) documented a lower incidence of participants reporting adverse events with tRNS compared to tDCS (6 participants vs. 13 participants, respectively), particularly concerning the symptom “itching” (7% of sessions vs. 13% of sessions, respectively). Similarly, Pena and colleagues also observed a higher overall occurrence of minor adverse events in the tDCS group compared to the tRNS group. These initial findings align with prior studies by Ambrus and colleagues (38), who suggested in their conclusions that future research should explore alternative methods to the sham condition (such as placebo itching) to ensure better blinding integrity.

### Limitations

While emphasizing the novelty of our approach and its rationale, we would also like to discuss some potential limitations.

First, to reduce the number of stimulation sessions per participant and streamline the study, we will not administer a sham session for both tDCS and hf-tRNS. In fact, half of the participants will receive a sham tDCS session, while the other half will receive a sham hf-tRNS session. However, we consider this limitation not to pose a significant bias, as both sham conditions entail identical placebo stimulation.

Second, the absence of neurophysiological measures, such as EEG, represent a limitation of the study. These measures could provide valuable insights into the underlying neurophysiological mechanisms of tDCS and hf-tRNS and help interpret the observed behavioral outcomes. Given the partial understanding of the neurophysiological effects of tES techniques, incorporating neurophysiological measures alongside behavioral assessments would be beneficial for future studies.

Finally, future studies should include a longitudinal monitoring of the effects of tES on reading abilities, with the aim of assessing the clinical relevance of experimental results.

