Both tDCS and tRNS are considered highly promising tES techniques for the pediatric population due to their favorable safety profile, high tolerability, versatility, ease of use, and low cost (26, 38–43). Interestingly, concerning safety and feasibility, both neurophysiological and behavioral studies [respectively (26, 36, 38)] showed that tRNS has higher skin perception thresholds, lower response rates to adverse events, and more effective blinding, making it a preferable option for the pediatric population.

The current study aims to investigate whether hf-tRNS is effective in improving reading abilities and whether it may outperform tDCS in specific reading aspects. The main goal is to compare the effects of a single online session of hf-tRNS, tDCS, and sham stimulation on text, word, and non-word reading accuracy and speed in children and adolescents with DD. This proof-of-concept study will also assess the safety, tolerability, and blinding parameters of both tES techniques and compare them.

If hf-tRNS proves to be at least as effective as tDCS in improving reading outcomes, these results would provide valuable insights for the development of multi-session hf-tRNS protocols as a potential treatment approach for individuals with DD.

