### Study design

The study will employ a within-subject, randomized, double-blind, and sham-controlled design. Clinical eligibility, including the dyslexia assessment, the neuropsychological assessment, and the psychopathological assessment will be evaluated on Day 0 (Baseline). Participants will be exposed to three conditions (Day 1, Day 2, Day 3): (A) a single active tDCS session; (B) a single active hf-tRNS session; and (C) a single sham tDCS or sham hf-tRNS session. Each condition will be separated from the other by a one-week interval to avoid carry-over effects (27). The ordering of conditions will be counter-matched among participants. After recruitment, participants will be allocated to one of six possible combinations of conditions (i.e., ABC, ACB, BAC, BCA, CBA or CAB). Stratified randomization will be performed by an independent researcher immediately after the participant completes the screening evaluation. This process will ensure assignment masking. Stratified randomization will use the minimal sufficient balancing method to prevent imbalances in baseline characteristics and will take into account participants’ demographics (e.g., age, IQ, and gender) and the severity of DD (calculated as the mean standard deviation between speed and accuracy in the text reading task) (45–48). The randomization information will be retained by an independent researcher until the data collection has been completed (Figure 1).

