### Sham tES conditions

To control for potential placebo effects, participants during the sham condition will undergo the same procedures as those in the active conditions (active tDCS, active hf-tRNS). This includes using the same electrode positioning and tRNS/tDCS equipment turn-on time (30 s). Apart from this short stimulation, during the sham condition participants will not receive the real stimulation (0 mA) for the rest of the session.

Among all participants, half of them will undergo a sham tDCS session (with the same electrode positioning and tDCS equipment turn-on time), while the other half will undergo a sham tRNS session (with the same electrode positioning and tRNS equipment turn-on time).

All participants, their families and the evaluators will be blinded to the stimulation conditions.

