### Statistical analyses and expected results

The Shapiro–Wilk test will be used to test the normality of the data and Levene’s test for the homogeneity of variances. When data will be normally distributed and the assumption of homogeneity will not be violated, parametric analyses will be computed. When one assumption will not be met, non-parametric tests will be conducted or a log-transformation of the distribution will be applied. Sphericity will be verified by Mauchly’s sphericity test and when not met, Greenhouse–Geisser correction will be applied.

Chi-Square analyses will be used to compare the groups on demographic and safety and blinding measures (categorical variables).

Covarying for age, a preliminary analysis to test the effect of the four repetitions (Day 0, Day 1, Day 2, and Day 3) of the reading tasks (accuracy and speed of TEXT, HF, LF, and NW) will be conducted.

RM-ANOVA will be used to compare reading measures (TEXT, HF, LF, and NW accuracy and speed), separately, with conditions (Day 0, A, B, C) as a within-subjects factor and age as covariate.

*Post hoc* comparisons will be assessed using Tukey’s honest significance test.

Partial eta squares (η_p_^2^) will be used as measures of effect sizes.

We hypothesize that:

hf-tRNS will be at least as effective as tDCS in improving TEXT reading accuracy compared with sham condition (primary outcome);hf-tRNS and tDCS will improve performance in the remaining reading tasks (TEXT reading speed and HF, LF, and NW reading accuracy and speed) compared with sham condition;hf-tRNS and tDCS will be as safe as sham condition (i.e., neither tDCS nor hf-tRNS will induce severe AEs or lead to dropouts due to intolerance to stimulation);the blinding will be kept across the conditions.

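### The two shams cannot be assumed identical for the blinding guess and sensation items, so these should also be reported by sham type

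*Protocol article*

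**What the plan says.** The Study design section defines one sham condition with two possible contents: "C) a single sham tDCS or sham hf-tRNS session". The Sham tES conditions section fixes the split: "half of them will undergo a sham tDCS session (with the same electrode positioning and tDCS equipment turn-on time"), while the other half have the tRNS equivalent. Both shams share electrode positions and a 30 s turn-on, and are then switched off: "Apart from this short stimulation, during the sham condition participants will not receive the real stimulation (0 mA) for the rest of the session".

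The Limitations section lists the split first among the limitations, explains that it spares each child an extra session, and dismisses it on the ground that "both sham conditions entail identical placebo stimulation".

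On how the two techniques feel, the Introduction says that "tRNS has higher skin perception thresholds, lower response rates to adverse events, and more effective blinding". The Discussion describes the one direct paediatric comparison as "demonstrating that tRNS is less perceptible and potentially preferable in pediatrics".

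On allocation, "participants will be allocated to one of six possible combinations of conditions", namely the orderings of A, B and C. Sham type is not part of an order and is not among the named balancing factors. The Statistical analyses section compares safety and blinding by chi-square, refers to sham as a single condition, and expects that "the blinding will be kept across the conditions".

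**The concern.** The reason given for pooling conflicts with the protocol's own rationale. Each sham begins with a short real stimulation of its own current type, direct current or random noise. Those current types are said to differ in skin perception, adverse-event reports and quality of blinding. If any of that difference shows within 30 s, the shams differ on the very items that the post-session questionnaire collects.

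At stake are the blinding hypothesis and the reading of the sensation and tolerability items against sham. A mixed comparator can make a well-blinded technique look poorly blinded, or hide real unblinding. A later check of one sham against the other would be hard to interpret if sham type happened to be uneven over the session orders.

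**Working it through.** **1. Children per sham type.** The only planned figure involved is the sample size of 24. It reproduces with f = 0.25, alpha = 0.05 and m = 4 repeated measurements, if the correlation is taken as rho = 0.5 with sphericity (neither is stated). Noncentrality = f² × N × m / (1 − rho) = 0.0625 × 24 × 4 / 0.5 = 12, on 3 and 69 degrees of freedom, gives power of 81.7%; N = 23 gives 79.7%. The sample size is not at fault here. Half of 24 leaves 12 children per sham type.

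**2. What pooling does.** Let pD and pR be the proportions who believe they had active stimulation after sham tDCS and sham tRNS, and aD and aR the proportions after each active technique. With an even split the pooled sham rate is S = (pD + pR)/2, so:

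- aD − S = (aD − pD) + (pD − pR)/2
- aR − S = (aR − pR) − (pD − pR)/2

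Each contrast is the matched one, shifted by half the gap between shams, with opposite signs.

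**3. Illustration, with assumed rates.** The documents give none for sham. Take pD = 60% and pR = 30%, so S = 45%.

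- Artefact: if each active technique exactly equals its own sham, tDCS appears 60 − 45 = 15 points above sham and hf-tRNS 45 − 30 = 15 points below it.
- Masking: if active hf-tRNS gives 45%, the true gap from its own sham is 45 − 30 = 15 points, but the pooled contrast is 45 − 45 = 0.

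Assumed gaps of 10 to 40 points give shifts of 5 to 20 points. Of 24 children, that is 24 × 0.05 = 1.2 to 24 × 0.20 = 4.8.

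**4. Can the data show that the shams are equivalent?** Not at 12 versus 12. On a continuous item, 80% power needs a standardised difference of about 1.20. On the guess, with 30% assumed for sham tRNS and 50, 60, 70 or 80% for sham tDCS, power is 16, 31, 50 or 72%.

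**5. Precision of matched comparisons.** Every child has both active sessions, so each technique can be paired with its own sham in 12 children. For a continuous item with an assumed standardised paired difference of 0.5, power is 35% with n = 12 against 65% with n = 24. The difference detectable at 80% power is 0.89 against 0.60.

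**6. Sham type over orders.** Assume four children per order and an unconstrained 12/12 split. All six orders then split 2:2 with probability 6⁶ / C(24,12) = 46,656 / 2,704,156 = 1.7%. In 100,000 simulated allocations, at least one order had only one sham type in 42%. Balancing sham type within order gives 6 × 2 = 12 cells of 24/12 = 2 children.

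**The case against.** The split is a disclosed and reasoned trade-off: it spares each child a fourth session. The perceptibility evidence, including the counts of 6 versus 13 participants with adverse events, concerns the techniques as delivered, not a 30 s turn-on, and the Discussion once hedges it. Nothing in the protocol reports that the two shams differ, and after the turn-on both are at 0 mA. All of this stands, so a reader who infers that the shams have been shown to differ goes beyond the text. What fails is the unqualified claim that they are the same.

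A reader might also infer that the safety comparison as a whole is compromised. It is not. The main safety question is tDCS against tRNS, which uses all children and no sham. The safety hypothesis is made concrete as no severe adverse events and no dropouts from intolerance, which hardly depends on the comparator.

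Nor does the article say that the halves are assigned non-randomly. It is silent, and a full protocol may settle the matter. The simulation in step 6 shows what an unconstrained split could do, not what was done. The chi-square sentence likewise does not forbid a breakdown by sham type.

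Finally, matched comparisons in 12 children are weak and could seldom confirm or refute blinding. That is a good reason to make them descriptive and additional, but not to omit them.

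**Conclusion.** The point holds in a limited form. The protocol cannot assume identical shams for the blinding guess and the sensation and tolerability items while describing the two current types as different on those features. Comparing each active technique with the pooled sham could create or mask a difference of up to half the gap between the shams. That gap is unknown and may be small; the 5 to 20 points rest wholly on assumed gaps of 10 to 40, and the halving rests on an even split.

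It would be wrong to read this as bias in the primary outcome. Reading is tested about 10 min into the session, when both shams have long been at 0 mA, so any direct effect there is probably small. This is a cheap improvement to the blinding and sensation reporting, not a threat to the main result.

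**What to change.** 1. In Limitations, withdraw the claim that the shams are identical and limit it to what they share: electrode positions, turn-on time and 0 mA afterwards.
2. Keep the pooled comparison, and add the blinding guess and the sensation and adverse-effect items by sham type: active tDCS against sham tDCS, and active hf-tRNS against sham hf-tRNS, each within the roughly 12 children who had both. Present these descriptively, with intervals.
3. For children not yet allocated, assign sham type at random and balanced within the six orders, or state that this is already done.
4. Keep the pooled sham as comparator for reading, with sham type as a term in one sensitivity analysis.

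No extra sessions or children are needed. The cost is some analysis wording and a revised allocation list that has to be reconciled with the minimal sufficient balancing on age, IQ, gender and severity. Enrolment began in August 2023, so balance may be achievable only for the remaining children. The matched comparisons will be imprecise and cannot confirm blinding.

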## Conclusion

In conclusion, the present study could provide new insights regarding the effectiveness of a newly-wave tES method never used in children and adolescents with DD, the hf-tRNS, potentially paving the way for further studies involving multiple hf-tRNS sessions. Considering the absence of studies evaluating the efficacy of hf-tRNS in improving reading skills and comparing it with the effects obtained with tDCS, we preferred to be cautious in advancing hypotheses of superiority of one technique over the other. However, while expecting comparable effects of the two techniques on outcome measures, we believe that this study may help optimize neuromodulation protocols for dyslexia in the future, for example, by considering the magnitude of the effects obtained by the two techniques. Of importance, this project will employ an experimental design that keeps the study burden for DD participants at a minimum, while providing key steps to understand which tES technique may be most effective for multi-session treatment applications.

The opportunity to compare tDCS and hf-tRNS in the same experimental setting, investigating whether differ in modulating reading performance and in terms of safety and tolerability, will be a valuable step forward to identify brain-directed treatments for DD. Instead, it will be crucial to assess whether the potential comparability on behavioral outcomes will go hand in hand with comparability on tolerability and safety parameters.

## Ethics statement

The study was approved by Bambino Gesù Children’s Hospital ethics committee (process number 2639_OPBG_2021). The study was conducted in accordance with the local legislation and institutional requirements. Written informed consent for participation in this study was provided by the participants’ legal guardians/next of kin.
